#### **4.1.1 Number of Centers**

Between 4 and 6 study centers will be selected for participation in the study.

#### **4.1.2 Definition of Treatment Cycle and Duration**

##### **4.1.2.1 Cycle Duration**

Each cycle will be 28 days.

##### **4.1.2.2 Treatment Phase**

Treatment will be continued until progression of disease according to IMWG criteria, unacceptable toxicities occur in individual subjects or consent is withdrawn. Cycles 1 through 4 are considered D-KRd induction cycles, Cycle 5-8 D-KRd consolidation, and Cycles 9-24 D-KRd maintenance cycles. After Cycle 4, subjects who are deemed candidates for ASCT will proceed to stem cell harvest as per institutional guidelines. However, the study design recommends a “delayed” transplant for ASCT candidates, as in subject having completed frontline KRd study without or with delayed transplant. This means that patients who are transplant candidates enrolled in this study will not proceed to ASCT; rather, they will have cells frozen down for a potential future transplant at progression or unacceptable toxicity after Cycle 4. After completion of stem cell harvest, patients will resume protocol treatment.

In the event that a subject’s risk status is unknown at the time of study entry, the subject will be required to re-consent to continue participation in this study if it is later determined that the subject has high-risk disease status and therefore may benefit from ASCT.

#### **4.1.3 End of Treatment Visit**

Patients that discontinue from treatment will undergo an end-of-treatment visit, regardless of the reason of discontinuation, 28 days after the last dose of study medication.

#### 4.1.4 Long Term Follow Up

Patients will be followed up every 3 months for progression and survival from the completion of the safety follow-up visit. Patients who progress during treatment will be followed for survival for 2 years from the completion of the safety follow-up visit or until death, whichever occurs first. The follow up can be done over the phone. For additional details on follow up duration see [Section 6.6.1](#).

## 5 Patient Selection

### 5.1 Inclusion Criteria

Subjects must meet all of the following inclusion criteria to be eligible to enroll in this study. No enrollment waivers will be granted.

1. Newly diagnosed, previously untreated myeloma requiring systemic chemotherapy
  - Prior treatment of hypercalcemia or spinal cord compression or active and/or aggressively progressing myeloma with corticosteroids or lenalidomide or bortezomib-based regimens does not disqualify the patient (the treatment dose should not exceed the equivalent of 160 mg of dexamethasone in a 4-week period or not more than 1 cycle of PI/IMiD-based therapy).
2. Both transplant and non-transplant candidates are eligible
3. Diagnosis of symptomatic multiple myeloma as per current IMWG uniform criteria prior to initial treatment
4. Monoclonal plasma cells in the BM  $\geq 10\%$  or presence of a biopsy-proven plasmacytoma
5. Measurable disease, prior to initial treatment including any emergent treatment of myeloma. Measurable disease will be indicated by one or more of the following:
  - Serum M-protein  $\geq 1$  g/dL
  - Urine M-protein  $\geq 200$  mg/24 hours
  - If serum protein electrophoresis is felt to be unreliable for routine M-protein measurement, then quantitative immunoglobulin levels are acceptable

- Serum Freelite measurable disease as per current IMWG criteria
6. Bone marrow specimen will be required at study entry; available DNA sample from pre-induction BM will be used for calibration step for MRD evaluation by gene sequencing
  7. Males and females  $\geq 18$  years of age
  8. ECOG performance status of 0-1
  9. Adequate hepatic function, with bilirubin  $\leq 1.5 \times \text{ULN}$  and aspartate aminotransferase (AST) and alanine aminotransferase (ALT)  $\leq 3 \times \text{ULN}$
  10. ANC  $\geq 1.0 \times 10^9/\text{L}$ , hemoglobin  $\geq 8 \text{ g/dL}$ , platelet count  $\geq 75 \times 10^9/\text{L}$
  11. Calculated creatinine clearance (by Cockcroft-Gault)  $\geq 50 \text{ mL/min}$  or serum creatinine below  $2 \text{ g/dL}$
  12. FCBP must have 2 negative pregnancy tests (sensitivity of at least  $50 \text{ mIU/mL}$ ) prior to initiating lenalidomide. The first pregnancy test must be performed within 10-14 days before and the second pregnancy test must be performed within 24 hours before lenalidomide is prescribed for Cycle 1 (prescriptions must be filled within 7 days).
  13. FCBP must agree to use 2 reliable forms of contraception simultaneously or to practice complete abstinence from heterosexual intercourse during the following time periods related to this study: 1) for at least 28 days before starting lenalidomide; 2) while participating in the study; and 3) for at least 90 days after discontinuation from the study.
  14. Male subjects must agree to use 1 highly-effective method of contraception and 1 effective method of contraception at the **same time** during sexual contact with females of childbearing potential while participating in the study and for at least 90 days following discontinuation from the study even if he has undergone a successful vasectomy.
  15. All study participants in the US must be consented to and registered into the mandatory Revlimid REMS® program and be willing and able to comply with the requirements of Revlimid REMS®.
  16. Voluntary written informed consent

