### **6.3 Study Drug Administration**

#### **6.3.1 Carfilzomib Administration**

Carfilzomib for injection is supplied as a lyophilized parenteral product in single-use vials. The lyophilized product is reconstituted with water for injection to a final carfilzomib concentration of 2.0 mg/mL prior to administration. The dose will be calculated using the subject's actual BSA at baseline. Subjects with a BSA  $> 2.2 \text{ m}^2$  will receive a dose based upon a  $2.2 \text{ m}^2$  BSA. Dose adjustments do not need to be made for weight gains/losses of  $\leq 10\%$ . Subjects with a Body Surface Area (BSA) of greater than  $2.2 \text{ m}^2$  will receive a capped dose of 44 mg of carfilzomib (at the  $20 \text{ mg/m}^2$  dose level), 59.4 mg of carfilzomib (at the  $27 \text{ mg/m}^2$  dose level), or 79.2 (at the  $36 \text{ mg/m}^2$  dose level).

Carfilzomib will be given as an IV infusion over 30 minutes on Days 1, 2, 8, 9, 15 and 16 of Cycles 1- 8 and Days 1, 2, 15 and 16 of Cycles 9-24, and must be administered prior to daratumumab. If the subject has a dedicated line for carfilzomib administration, the line must be flushed with a minimum of 20 mL of normal saline prior to and after drug administration. The dose will be administered at a facility capable of managing hypersensitivity reactions. Subjects will be pre-hydrated with 250mL normal saline or other appropriate IV fluid formulation on cycle 1 Day 1. Other hydration procedures will be optional and per the discretion of the treating investigator. Subjects will remain at the clinic under observation for at least 1 hour following each dose of carfilzomib in Cycle 1 and following the dose on Cycle 2, Day 1. Subjects should be monitored periodically during this period for evidence of fluid overload. Serum chemistry values, including creatinine, must be obtained and reviewed prior to each dose of carfilzomib during Cycles 1 and 2. Refer to [Table 6-8](#) for guidance regarding dose reduction in subjects with compromised renal function.

Doses of carfilzomib may be rescheduled up to 2 days if the scheduled day falls upon a holiday or with approval from the Lead Principal Investigator. If Day 2 of Carfilzomib dosing is delayed (i.e., Day 2, 9, 16) 4 mg of dexamethasone premedication is required to be used prior to second treatment. Missed doses will not be replaced during a cycle. Carfilzomib will be escalated from  $20 \text{ mg/m}^2$  (Cycle 1 Days 1 and 2)

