**Table 6-8 Dose Modifications for Non-hematologic Toxicity**

| Recommended Action              |                                                                                                       |                                                                                |
|----------------------------------------|-------------------------------------------------------------------------------------------------------|--------------------------------------------------------------------------------|
|                                        | Lenalidomide                                                                                   | Carfilzomib                                                             |
| Grade 4 neuropathy              | Discontinue                                                                                           | Discontinue                                                                    |
| Renal dysfunction               |                                                                                                       |                                                                                |
| Serum creatinine > 2 mg/dL             | Base dose reduction on calculated GFR (below)                                                         | Base dose reduction on calculated GFR (below)                                  |
| CrCl > 50 mL/min                       | Full dose                                                                                             | Full dose                                                                      |
| CrCl < 50 mL/min
> 30 mL/min        | Reduce lenalidomide to 10 mg every 24 h; may reinstate prior dose if, after 2 cycles, CrCl normalizes | Full dose                                                                      |
| CrCl < 30 mL/min                       | Reduce lenalidomide to 15 mg every 48 h                                                               | Hold carfilzomib until CrCl > 30 mL/min; restart at 1 dose decrement           |
| CrCl < 30 mL/min
requiring dialysis | 5 mg. Once daily. On dialysis days the dose should be administered following dialysis.                | Hold until resolved to ≤ Grade 2. Then restart carfilzomib at 1 dose decrement |

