#### **Sub-classification**

- a. Serum creatinine <2.0 mg/dL
- b. Serum creatinine >2.0 mg/dL

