### B. International Myeloma Working Group International Staging System (ISS)

1. Stage I: B2M < 3.5 plus serum albumin  $\geq 3.5$  (med S 62m)
2. Stage II: B2M < 3.5 but serum alb. < 3.5 OR B2M 3.5 - < 5.5 (med S 44m)
3. Stage III: B2M  $\geq 5.5$  (med S 29m)
4. Sub-classify stages 1+2 according to cr< or  $\geq 2$  and stage 3 according to low platelets (< 130k) or high LDH

IMWG criteria for symptomatic myeloma:

All three criteria must be met:

1. Clonal bone marrow plasma cells and/or documented clonal plasmacytoma
  2. Presence of serum and/or urinary monoclonal protein
  3. Evidence of end-organ damage that can be attributed to the underlying plasma cell proliferative disorder, specifically:
    - a. Hypercalcemia: serum calcium  $\geq 11.5$  mg/dL or
    - b. Renal insufficiency: serum creatinine >2mg/dL or
    - c. Anemia: hemoglobin at least 2 g/dL below the lower limit of normal or a hemoglobin <10 g/dL or
- Bone lesions: lytic lesions, osteopenia or pathologic fractures

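### Inclusion criterion 11 gives the serum creatinine limit in g/dL instead of mg/dL, so read literally it excludes nobody on renal function

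*Protocol*

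**What the plan says.** Section 5.1, item 11, sets the only renal entry requirement. A patient qualifies with Cockcroft-Gault clearance of at least 50 mL/min "or serum creatinine below" 2 g/dL. The list opens with the statement "No enrollment waivers will be granted". No criterion in Section 5.2 sets a renal limit.

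Elsewhere the same threshold is in mg/dL:

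- Table 6-8, renal rows: "Serum creatinine > 2 mg/dL", with the instruction "Base dose reduction on calculated GFR (below").
- Appendix 1, Durie-Salmon sub-classification: "Serum creatinine <2.0 mg/dL".
- Appendix 1, IMWG criteria for symptomatic myeloma: "Renal insufficiency: serum creatinine >2mg/dL".

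On dosing, the Table 6-8 row for clearance below 30 mL/min reads, for carfilzomib, "Hold carfilzomib until CrCl > 30 mL/min; restart at 1 dose decrement", and it cuts lenalidomide to 15 mg every 48 hours. Section 6.3.1 sends the reader to that table "for guidance regarding dose reduction in subjects with compromised renal function", and Section 6.7.4 does the same. Section 6.7.4 also says that carfilzomib is not fully characterized below 30 mL/min.

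**The concern.** An eligibility threshold has to be usable as printed. It is copied into the checklist, and Section 5.3.1 requires source documents for each criterion. A creatinine limit that no patient can fail, joined to the clearance limit by 'or', switches off the whole renal criterion when followed literally.

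A second matter remains once the unit is corrected. With 'or' kept, creatinine below 2 mg/dL qualifies a patient at any clearance. Creatinine is a weak guide to clearance in older and lighter patients, so some could enter below 30 mL/min, the level at which Section 6.7.4 urges caution and Table 6-8 has its hold row. It should be clear to a site whether such a patient is to be treated or held at the first dose.

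**Working it through.** **Unit.** The input is the limit of 2 g/dL in item 11. Conversion: 2 g/dL × 1000 mg/g = 2000 mg/dL. Ratio to the value used in Table 6-8 and Appendix 1: 2000 / 2 = 1,000.

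To see what the printed limit would mean, put it into Cockcroft-Gault:

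clearance = (140 − age) × weight in kg × (0.85 if female) / (72 × creatinine in mg/dL)

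For a man of 60 years and 80 kg (assumed) at 2000 mg/dL: 80 × 80 / (72 × 2000) = 6400 / 144,000 = 0.04 mL/min. No candidate reaches that level, so every candidate meets the creatinine condition and therefore item 11 as a whole.

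**Item 11 read as 2 mg/dL.** The age, weight and creatinine values below are assumptions chosen to show what the rule permits; the protocol gives no distribution of any of them.

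| Patient | Creatinine (mg/dL) | Calculation | Clearance (mL/min) |
|---|---|---|---|
| Woman, 75 y, 60 kg | 1.9 | 65 × 60 × 0.85 / (72 × 1.9) = 3315 / 136.8 | 24.2 |
| Man, 70 y, 60 kg | 1.99 | 70 × 60 / (72 × 1.99) = 4200 / 143.28 | 29.3 |
| Man, 65 y, 80 kg | 1.99 | 75 × 80 / (72 × 1.99) = 6000 / 143.28 | 41.9 |

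All three fail the 50 mL/min condition and qualify through creatinine alone. The first two are below 30 mL/min; the third, heavier and younger, is not. The woman in the first row reaches 30 mL/min at a creatinine of 3315 / (72 × 30) = 3315 / 2160 = 1.53 mg/dL, so for her the range from about 1.53 to just under 2 mg/dL means eligibility with clearance below 30.

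**What the dosing text then says about her.** Two readings of Table 6-8 are open:

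- The clearance rows stand alone. Carfilzomib is held from the first dose, and a stable clearance of 24 mL/min may never meet the restart condition.
- The creatinine row above 2 mg/dL is the gate to the clearance rows. At 1.9 mg/dL she does not enter them, and she is treated.

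The first reading is the more natural one, because Sections 6.3.1 and 6.7.4 point to the table for compromised renal function in general. Three other places lean towards the second. Section 6.5 presents the tables as managing toxicity. Section 6.4 asks only that creatinine return to baseline in Cycles 1 and 2. Section 1.5.2.1 reports a phase 1 study in which carfilzomib was given safely below 30 mL/min, dialysis included, without dose adjustment.

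**The case against.** The best answer on the unit is that nobody would apply 2 g/dL literally. Section 5.3.1 has the Lead Principal Investigator or a designee approve every patient's eligibility and allows criteria to be clarified, so reading mg/dL needs no waiver. That stands, and it limits the practical effect. It does not make the printed figure right: the threshold is operative and is wrong by a factor of 1,000.

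A reader might infer that patients with severe renal failure were freely enrolled. The protocol does not support that, given the evident meaning of item 11 and the central approval of eligibility.

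On the missing floor, a reader might infer that eligibility contradicts the dosing table. The text does not establish this. The creatinine row in Table 6-8 can act as a gate. Section 1.5.2.1 supports treating below 30 mL/min. Table 6-8 has rows for reduced clearance and dialysis, and Section 6.7.3 names clearance below 50 mL/min as a tumor lysis risk, so impaired patients were foreseen. Qualifying for a trial and then having a drug held under its dosing rules is not in itself a contradiction. Exclusion 24, which leaves clinically significant conditions to the investigator's judgment, is a further partial safeguard. This half is therefore a suggestion.

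A reader might also want an expected number of such patients among the 45. Any such number would come wholly from assumed ages, weights and creatinine values, and from an assumed relation between weight and creatinine. ECOG 0-1 and the frailty exclusion would lower it by an unknown amount. None is given here.

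**Conclusion.** The unit in item 11 is wrong. As printed, the creatinine limit is 2000 mg/dL and the criterion excludes nobody on renal function; the value used elsewhere in the protocol is 2 mg/dL. This conclusion needs only unit conversion and the word 'or'.

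The absence of a clearance floor at 2 mg/dL is real, as the 24.2 mL/min example shows, but it is a design choice that the sponsor may keep. What is worth settling is whether the Table 6-8 hold applies to a patient who enters with stable clearance below 30 mL/min and creatinine below 2 mg/dL. The example rests on assumed patient values and shows what is possible, not how often it happens.

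Severity is minor. The primary test and the sample size do not depend on item 11. Section 6.3.5 says there will be no new starts, which suggests that accrual is closed; in that case the correction is to the record only.

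**What to change.** In Section 5.1, item 11, replace g/dL with mg/dL, and make the same change in the eligibility checklist.

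As an optional alignment, choose one of two:

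- Add to item 11 that Cockcroft-Gault clearance must be at least 30 mL/min in all cases, in line with the limit in Table 6-8.
- If the sponsor means to treat such patients on the strength of the study cited in Section 1.5.2.1, add a note to Table 6-8 that the hold below 30 mL/min does not apply to stable baseline impairment with creatinine below 2 mg/dL.

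The cost is one unit, one clause or note, and a checklist update. The floor would make any patient below 30 mL/min ineligible; the note would exclude no one. If enrolment has ended, an erratum is enough.

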## 5.2 Exclusion Criteria

Patients meeting any of the following exclusion criteria are not eligible to enroll in this study. No enrollment waivers will be granted.

1. Frail non-transplant candidates, defined as in Palumbo et al, Blood 2015
2. Non-secretory or hyposecretory multiple myeloma, prior to initial treatment defined as <1.0 g/dL M-protein in serum, <200 mg/24 hr urine M-protein, and no measurable disease as per IMWG by Freelite®
3. POEMS syndrome (polyneuropathy, organomegaly, endocrinopathy, monoclonal protein, and skin changes)
4. Amyloidosis
5. Plasma cell leukemia
6. Waldenström's macroglobulinemia or IgM myeloma
7. Radiotherapy to multiple sites or immunotherapy within 4 weeks before start of protocol treatment (localized radiotherapy to a single site at least 1 week before start is permissible)
8. Participation in an investigational therapeutic study within 3 weeks or within 5 drug half-lives ( $t_{1/2}$ ) prior to first dose, whichever time is greater
9. Patients not able to tolerate daratumumab, carfilzomib, lenalidomide or dexamethasone
10. Peripheral neuropathy  $\geq$  Grade 2 at screening
11. Diarrhea > Grade 1 in the absence of antidiarrheals
12. CNS involvement
13. Pregnant or lactating females
14. Major surgery within 3 weeks prior to first dose

15. Myocardial infarction within 6 months prior to enrollment, NYHA Class III or IV heart failure, uncontrolled angina, severe uncontrolled ventricular arrhythmias, or electrocardiographic evidence of acute ischemia or active conduction system abnormalities
16. Prior or concurrent pulmonary embolism
17. Known moderate or severe persistent asthma or known chronic obstructive pulmonary disease (COPD)
  - a. Known or suspected chronic obstructive pulmonary disease (COPD) with a forced expiratory volume in 1 second (FEV1) <50% of predicted normal
  - b. Moderate or severe persistent asthma within the past 2 years, or currently has uncontrolled asthma of any classification. Note that subjects who currently have controlled intermittent asthma or controlled mild persistent asthma are allowed in the study.
18. Rate-corrected QT interval of electrocardiograph (QTc) > 470 msec on a 12-lead ECG during screening
19. Uncontrolled hypertension or diabetes
20. Acute infection requiring systemic antibiotics, antivirals, or antifungals within two weeks prior to first dose
21. Known seropositive for or active viral infection with human immunodeficiency virus (HIV) or hepatitis C virus (HCV)
22. Seropositive for hepatitis B (defined by a positive test for hepatitis B surface antigen [HBsAg]). Subjects with resolved infection (ie, subjects who are HBsAg negative but positive for antibodies to hepatitis B core antigen [anti-HBc] and/or antibodies to hepatitis B surface antigen [anti-HBs]) must be screened using real-time polymerase chain reaction (PCR) measurement of hepatitis B virus (HBV) DNA levels. Those who are PCR positive will be excluded. EXCEPTION: Subjects with serologic findings suggestive of HBV vaccination (anti-HBs positivity as the only serologic

marker) AND a known history of prior HBV vaccination, do not need to be tested for HBV DNA by PCR.

23. Non-hematologic malignancy or non-myeloma hematologic malignancy within the past 3 years except a) adequately treated basal cell, squamous cell skin cancer, thyroid cancer, carcinoma in situ of the cervix, or prostate cancer < Gleason Grade 6 with stable prostate-specific antigen levels or cancer considered cured by surgical resection alone.
24. Any clinically significant medical disease or condition that, in the investigator's opinion, may interfere with protocol adherence or a subject's ability to give informed consent.

### **5.3 Subject Enrollment and Registration**

#### **5.3.1 Registration Process**

Prior to registration and any study-specific evaluations being performed, all patients must have given written informed consent for the study and must have completed the pre-treatment evaluations. Patients must meet all of the eligibility requirements listed in [Section 5](#).

Registration will happen separately between the sites. All patients who have signed consent, regardless of if they are enrolled or not, will be entered into the University of Chicago Clinical Trials Management database, eVelos, within 24 hours of signing consent. Subjects will be assigned a unique subject number that will remain consistent for the duration of the study. Sites should make all enrollment requests at least 72 hours before the anticipated start date of Cycle 1 Day 1. Screening and on-treatment assessments are expected to be entered into eVelos within two weeks of study required visits.

The Lead PI or designee will be responsible for approving the eligibility of all patients at corresponding sites. Specifically, once all required screening assessments have been performed, the information will have to be reviewed by the Lead Principal Investigator or designee. When the subject's study eligibility has been confirmed by the Lead Principal Investigator or designee, they or authorised site staff, will finalize data entry into eVelos. Treatment may not start until the approved enrollment form is sent back to the site.

When a potential patient has been identified, notify the CRA via phone or email to ensure a reservation on the study: [REDACTED]. Reservations for potential subjects will only be held for subjects who have signed consent for that particular study.

When registering a subject, the following must occur:

- Confirm that the institution has a current IRB approval letter for the correct version of protocol/consent and has an annual update on file, if appropriate.
- Submit all required materials (eligibility checklist, source documentation, and full copy of the signed informed consent form) to confirm eligibility and required pre-study procedures to the CRA a minimum of 48 hours prior to the subject's scheduled therapy start date.
- Source documentation includes copies of all original documents that support each inclusion/exclusion criteria. The eligibility checklist does not serve as source documentation but rather as a checklist that original source documentation exists for each criterion.
- Communicate with the CRA to ensure all necessary supporting source documents are received and the potential subject is eligible to start treatment on schedule. If there are questions about eligibility, the CRA will discuss it with the Lead PI. Lead PI may clarify, but not overturn, eligibility criteria.
- Affiliate sites must confirm registration of subjects by obtaining a subject study ID number from the CRA via phone, fax or email.
- If a subject does not start on the scheduled Day 1 treatment date, promptly inform the CRA as the delay in start may deem the subject ineligible and/or require further or repeat testing to ensure eligibility.
- The date the patient's eligibility is confirmed by the CRA will be considered the patient's "Enrolled/On Study Date." The patient's subject ID will be assigned and a confirmation of registration will be issued by the Lead Site CRA on this date. Subjects that sign consent and do not go "On Study" will be recorded in the database as "Not Enrolled" with the date they signed consent and the reason they were not enrolled (e.g., Ineligible, Screen Failure or Withdrawn Consent).

